#### Blinding

Participants will be not be blinded to group allocation as the intervention arm involves weekly one-to-one sessions with the Treating Therapist at the respective study site. Following randomisation via the online web-based system (www.redcapcloud.com) the treating therapist is informed via e mail of the group allocation. The Treating Therapists and health care providers are also unable to be blinded due to the nature of the programmes. However, the Research Therapists undertaking the outcome assessments will be blinded to the participants’ allocated group.

The initial baseline assessment will be undertaken prior to randomisation ensuring these assessments are blinded. Every effort will be made throughout to ensure that subsequent assessments are blinded, for example by reminding participants at the start of the visit not to discuss their exercises or physiotherapy with the blinded Research Therapist. At each assessment time point, the blinded Research Therapists will be asked to record on the case report form (CRF) whether or not they have been un-blinded to group allocation, and if so the reason for this. In cases where Research Therapists were not un-blinded they will be asked to guess the group allocation for each participant.

### Interventions: randomised controlled trial

#### Generic booklet-based VR (control group)

The generic VR exercise group will undertake a one-hour individualised physiotherapy session during which they will receive the validated self-management booklet ‘Balance Rehabilitation’ [61]. The booklet explains how VR exercises help to improve vestibular symptoms and provides instructions on how to conduct the exercises. The Treating Therapist will provide further verbal instructions on how to use the booklet. Participants will be asked to practise the exercises unsupervised at home for 10 min, twice a day for 12 weeks and to fill out a daily diary sheet indicating treatment duration and content. They will receive telephone support from the Treating Therapist in the form of two 15 min phone calls, one in week 1 and one in week 4. These contacts will be guided by an interview schedule and focus on adherence, barriers to adherence and discussion of any concerns and queries regarding the exercise programme.

#### Customised VR (intervention group)

The customized vestibular rehabilitation group will receive 12 individualised, 1 h, vestibular rehabilitation sessions over a 12 week period, typically on a weekly basis. Sessions will be supervised by the Treating Therapist. Each participant will practice a selection from the following type of exercises:
Eye, head, and postural exercises that provoke a patient’s symptomsGaze stabilization exercisesExercises to re-train postural alignment and movement strategiesRe-training sensory strategiesLearning to adapt postural strategies to changing contextsDual task training while walkingPostural orientation exercisesNeuromuscular (ankle-hip-stepping motor strategies) postural strategies.

The exercises will be determined following an initial clinical assessment of oculomotor function, balance and mobility based on subjective report and objective tests of the VOR and eye-head coordination, the mini balance evaluation system test (mini-BEST test) [62], motion sensitivity quotient test [63], the gait assessment and intervention tool (G.A.I.T) [64] and a visual assessment of postural alignment. The Treating Therapist will select exercises in partnership with the participant during the supervised session. Progress in specific areas will be objectively assessed at each supervised session, any concerns will be discussed, exercises that have not yet been included in the home programme added and practised, and existing exercises modified to gradually increase task difficulty. Each participant will be provided with an individualised home exercise programme of 3–5 exercises to practise each for 1-min, twice daily on days they do not have a session with the therapist. This will include video links to a demonstration of the exercise and progression rules. For those with any reported symptoms of migraine, at first, three exercises only will be provided but progressed to five exercises if no noticeable exacerbation of symptoms beyond the exercise period is noted. Exercises will target vestibular-related symptoms; for example, if VOR is affected, gaze stabilisation training will always be included. One out of the five exercises can target other systems deemed relevant (by the Treating Therapist or participant) to balance and mobility (e.g. mobilisation or stretches for reduced neck motion). At the last supervised session, a home maintenance exercise programme will be provided.

#### Adherence and standardisation / fidelity to the interventions

Both groups of participants will be asked to complete a daily diary to record the duration of home exercise practice. This data will be reported as percentage completion of prescribed exercises. In addition, adherence in the customised group will be reported as the number of face-to-face sessions the participant attended.

The Treating Therapists based at the two sites will be responsible for delivering the interventions. Therapists will attend a 2 day training course at the start of the trial which will cover the theory and practice of vestibular rehabilitation, trial methods and the importance of adhering to protocol. The Treating Therapists will complete a standardised proforma outlining the exercises taught in both groups, the agreed frequency of training as well as advice provided in the one-to-one or telephone follow ups. This will enable assessment of intervention fidelity and potential contamination effects.

#### Data collection and outcome measures

Participant characteristics including demographics, type of MS, medication and co-morbidities will be documented at baseline using a customised CRF. Participants will additionally have a clinical screen for vestibulopathy [29, 65, 66]. This includes HINTS (the head impulse sign, presence and type of nystagmus and skew deviation) and truncal ataxia [29, 65, 66]. Potential factors affecting balance and mobility [67**]****,** including objective measures of isometric knee extensor strength (assessed in sitting using a strain gauge), distal leg sensation (as determined by 10 g monofilaments), reaction time (using an online program https://faculty.washington.edu/chudler/java/redgreen.html) and neck passive range of motion (using goniometry), will also be assessed.

Standardised and validated clinician-rated assessments and patient self-reported clinical outcomes will be measured at baseline prior to randomisation (T0). Baseline measurements and randomisation (T0) occurs 2 weeks prior to the participant commencing an intervention. Measures will also be taken post-intervention at 14 weeks (+/− 2 weeks) post-randomisation (T14) and 26 weeks (+/− 2 weeks) post-randomisation (T26).

#### Primary outcome measure

The primary outcome measure is the impact of dizziness on daily function assessed using the DHI at the primary endpoint of 26 weeks (+/− 2 weeks) post-randomisation, and will also be collected at the secondary endpoint of 14 weeks (+/− 2 weeks) post-randomisation [58]. The DHI is a validated 25-item self-report questionnaire that assesses three domains: functional, emotional and physical. Responses to each question are graded 0 (no), 2 (sometimes) or 4 (yes). The scores per section are summed to give a maximum score of 100 points. Higher scores indicate a greater perceived impact of dizziness. The DHI is reliable in people with MS (intraclass correlation coefficient = 0.90, 95% confidence limits 0.77–0.96) [68].

The primary economic endpoint is the quality-adjusted life-year (QALY) assessed using the EQ-5D-5L [69]. QALY weights will be derived using the ‘cross-walk’ [70] to the EQ-5D-3L UK tariff [71], as recommended by the National Institute for Health and Care Excellence (NICE) [72].

#### Secondary outcome measures

The following outcomes are assessed at both T14 and T26:
Functional ambulation using the Dynamic Gait Index [68, 73–75]Static and dynamic visual acuity assessed using an Early Treatment Diabetic Retinopathy Study (EDTRS) chart with and without passive head motion (40^0^ yaw rotation at 1.5 Hz) [76, 77]Visual dependency assessed using the Rod and Disc test [78, 79]Cognitive impairment and processing speed assessed using the Symbol Digit Modalities Test (SDMT) [80]Impact of MS on walking assessed using the 12 item self-report walking scale (MSWS-12) Version 2.0 [81]Perceived confidence in performing activities of daily living assessed using the self-report Activities-Specific Balance Confidence Scale [82]Self-reported symptoms of poor balance and increased anxiety and arousal assessed using the Vertigo Symptom Scale- Short Form [59, 83]Symptoms of visually induced dizziness symptoms assessed using the self-report Situational Characteristic Questionnaire [52]Fatigue as assessed using the self-report Fatigue Scale for Motor and Cognitive functions (FSMC) [84]Symptoms of depression and anxiety assessed using the self-report Hospital Anxiety and Depression Scale (HADS) [85]Health-related quality of life using the 29-item Multiple Sclerosis Impact Scale (MSIS-29) Version 2.0 [86], a disease specific patient-reported outcome measure [87]QALYs assessed by the Multiple Sclerosis Impact Scale – eight dimensions (MSIS-8D) and the Multiple Sclerosis Impact Scale – Eight Dimensions Patient version (MSIS-8D-P) [88, 89]. Both measures are based on responses to the MSIS-29, and will be used in sensitivity analysesRetrospective diary of falls over the past month for baseline measure and prospective daily falls diary over 12 weeks for assessment 2 (T14) and follow up (T26)Treatment adherence as determined by the use of patient reported diaries and reported as the percentage of completed prescribed exercises and attendance at face to face sessionsUser experience of the intervention will be explored through brief semi-structured face to face individual exit interviews based on an interview schedule.

### Safety monitoring

Participants will be monitored for adverse events via completion of adverse events forms, during telephone or face-to-face contacts as part of the intervention phase and during follow-up assessments. New or worsening problems which participants perceive to be related to participation in VR, as well as any relapses and falls, will be reported. If a member of the research team becomes aware of a severe adverse event, they will report this to the Chief Investigator within 24 h, and the trial sponsor will be informed. The Trial Management Group and the Trial Steering Committee will be informed of the details of all adverse events. There are no special compensation arrangements for harm arising from the study although neglectful harm will be covered by the insurance scheme of the sponsor organisation.

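### Programme-phase adverse events are asked about at treatment contacts, 12 in the customised arm and 3 in the booklet arm, so a by-arm event table is at risk of a spurious excess in the customised arm

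*Protocol article*

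**What the plan says.** Under Safety monitoring, the protocol article has adverse-event forms completed "during telephone or face-to-face contacts as part of the intervention phase and during follow-up assessments". The same section defines what is reportable: "New or worsening problems which participants perceive to be related to participation in VR, as well as any relapses and falls, will be reported".

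The intervention-phase contacts are set out under the two intervention headings. Customised VR (intervention group): participants "will receive 12 individualised, 1 h, vestibular rehabilitation sessions over a 12 week period, typically on a weekly basis". Generic booklet-based VR (control group): "The generic VR exercise group will undertake a one-hour individualised physiotherapy session", followed by telephone support "in the form of two 15 min phone calls, one in week 1 and one in week 4". Those calls "focus on adherence, barriers to adherence and discussion of any concerns and queries regarding the exercise programme"; adverse events are not named as a topic there.

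Some capture is common to both arms. Both attend T14 and T26 (Data collection and outcome measures). Falls are recorded prospectively in a daily diary (Secondary outcome measures). For home practice, "Both groups of participants will be asked to complete a daily diary" (Adherence and standardisation / fidelity to the interventions).

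Participants are not blinded, and they are reminded not to talk about their exercises or physiotherapy with the blinded assessor (Blinding). The steering committee monitors adverse-event reports and may look at unblinded data if events seem more frequent than expected (Trial management and oversight committees).

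**The concern.** During the programme, how often a participant is asked about adverse events depends on the arm. A customised participant meets the treating therapist about once a week. A booklet participant has no scheduled contact after the week 4 call until T14. Apart from relapses and falls, an event becomes reportable when the participant believes that VR caused it. Frequent contact with a therapist gives more prompts both to remember a problem and to link it to the exercises.

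Two uses of the data are exposed. A table of adverse events by arm could suggest that customised VR is less well tolerated when the true rates are equal. The steering committee could see the same artefact in unblinded data while it advises on whether the trial continues. In addition, problems that arise in the booklet arm after week 4 may come to light late.

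**Working it through.** **Inputs.** Customised arm: 12 sessions over 12 weeks, about weekly. Booklet arm: 1 session and 2 calls, in weeks 1 and 4. The programme starts 2 weeks after randomisation, so T14 falls at programme week 12. The plan states no safety figure to reproduce.

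**Contacts.** Booklet: 1 + 2 = 3. Treatment contacts are 12 against 3, a ratio of 4. With T14 and T26 added they are 14 against 5, a ratio of 2.8. The longest gap in the booklet arm is 12 − 4 = 8 weeks. The ±2-week window at T14 makes it 6 to 10 weeks.

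**Delay to the next enquiry.** Place customised sessions at programme weeks 0, 1, …, 11, booklet contacts at weeks 0, 1 and 4, and T14 at week 12 (the exact placement is an assumption). The gaps are then twelve of 1 week in the customised arm, and 1, 3 and 8 weeks in the booklet arm. For events spread evenly over 12 weeks, the mean delay is Σg² / (2 × 12):

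- customised: 12 / 24 = 0.5 weeks
- booklet: (1 + 9 + 64) / 24 = 3.1 weeks

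The share of the programme that is followed by a further treatment contact is 11/12 = 92% against 4/12 = 33%. The remainder rests on T14.

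**Effect on reported events.** Assume equal true rates, and a probability of reporting at the next enquiry that halves with every h weeks of delay. The mean reporting probability is

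(1/12) × Σ (h / ln 2) × (1 − 2^(−g/h)), summed over the gaps g.

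For h = 4, h / ln 2 = 5.771:

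- customised: 5.771 × (1 − 0.8409) = 0.918
- booklet: (5.771 / 12) × (0.1591 + 0.4054 + 0.7500) = 0.632
- ratio: 1.45

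| Assumed half-life h (weeks) | Customised | Booklet | Ratio |
|---|---|---|---|
| 2 | 0.845 | 0.451 | 1.87 |
| 4 | 0.918 | 0.632 | 1.45 |
| 8 | 0.958 | 0.781 | 1.23 |
| 16 | 0.979 | 0.879 | 1.11 |
| perfect recall | 1.000 | 1.000 | 1.00 |

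As an illustration, with an assumed true proportion of 40% and h = 4, the reported proportions are 0.40 × 0.918 = 37% and 0.40 × 0.632 = 25%.

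The documents give no recall figure, so the range is illustrative and is not a bound; h = 1 would give 2.53. In the other direction, events between T14 and T26 are asked about on the same schedule in both arms, so a table over all 26 weeks would show a smaller ratio than the programme-phase figures above.

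**The case against.** The strongest reply is that no between-arm safety comparison is stated. The objectives, outcome list and analysis sections contain no adverse-event endpoint or test, and tabulation can be left to the SAP. Both arms are asked at T14, about when the programme ends, and again at T26. Relapses and falls escape the relatedness filter, and falls have their own diary. The article does not say who holds the adverse-event forms, and the full protocol may. Most of this stands, and it limits the point. It does not remove it, because the stated mechanism still ties programme-phase enquiry to treatment contacts.

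Four stronger readings are tempting, and the documents do not support them:

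- A reader might infer that the safety results are biased and will show more events in the customised arm. With full recall at T14 the ratio is 1.0, so this is a risk and not a certainty.
- A reader might take the 4-fold ratio of contacts as a 4-fold ratio of events. Because T14 picks up part of what was missed, the modelled ratio is well below 4.
- A reader might assume that events are reported only if asked about within a week, and conclude that 100% against 25% are captured before T14. Strictly before T14 that rule gives 11/12 (92%) against 2/12 (17%); 12/12 against 3/12 arises only when T14 itself is counted. The rule also supposes that nothing older than a week is ever reported, which nothing in the article says.
- A reader might suppose that every event passes through the participant's view of its cause. Relapses and falls do not.

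One consideration runs the other way. If the blinded assessor also takes adverse events at T14, the reminder not to discuss exercises could discourage reports of VR-related problems, and the booklet arm relies most on that visit. The article does not say who asks, so this remains an inference.

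**Conclusion.** The point holds as a risk of unequal ascertainment. It mainly concerns new or worsening problems other than relapses and falls that are forgotten or not volunteered by T14. Relapses are exposed to a lesser extent, since they are exempt from the relatedness filter but have no diary. Falls are largely protected.

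Under equal true rates, evenly spread events and the contact times assumed above, customised participants would report about 1.1 to 1.9 times as many programme-phase events for recall half-lives of 16 to 2 weeks. The by-arm adverse-event table and the steering committee's unblinded review are affected; the primary DHI analysis is not. The change is worth making because an instrument that both arms already complete can remove most of the imbalance.

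**What to change.** - Add an adverse-event line to the daily diary in both arms, to be completed every day, including days when customised participants attend a session and do no home practice.
- At T14 and T26, put the same structured adverse-event questions to both arms, regardless of whether the participant thinks the problem is related to VR. Use a self-completed form that does not pass through the blinded Research Therapist, so that the answers do not reveal allocation.
- State that any between-arm summary uses diary-recorded events plus the T14 and T26 answers. List events captured only at treatment contacts separately and do not compare them between arms. Give the steering committee the same split.
- Report diary completion by arm, since weekly sessions may themselves encourage completion.

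Recruitment was under way when the article was published. For participants who have already passed the programme phase, the between-arm summary would have to rest on T14 and T26 reports alone, and the report should say so.

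The cost is one diary line, one short form and a reporting rule, with a few more minor events to process and slightly more diary burden. The interventions, the contact schedule and the primary analysis do not change.

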### Trial management and oversight committees

Two committees are involved in trial setup, management and oversight: The Trial Management Group (TMG) and the Trial Steering Committee (TSC). The TMG consists of members of the research team with representation from the CTU and the trial Sponsor. The TMG meets approximately monthly and oversees the general management of the trial and release of the trial results and publications. The TSC consists of members who are mainly independent of the sponsors and investigators (chair, external statistician and lay member). The TSC meets approximately every 6 months and will monitor reports of adverse events, recruitment and attrition rates, the project timeline and finances. It has the ability to see unblinded adverse event data if it is perceived that the frequency of events is higher than anticipated and advise on trial progression.

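### Outside severe events, relapses and falls, whether an adverse event is reported depends on an unblinded participant linking it to VR, so event counts mix occurrence with attribution.

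*Protocol article*

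**What the plan says.** All of the following is from the protocol article.

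- **Collection (Safety monitoring).** "Participants will be monitored for adverse events via completion of adverse events forms, during telephone or face-to-face contacts"; follow-up assessments are a further occasion.
- **What is reported (same section).** "New or worsening problems which participants perceive to be related to participation in VR, as well as any relapses and falls, will be reported". Relapses and falls carry no condition on cause. Other problems carry the condition that the participant sees a link with VR.
- **Severe events (same section).** "If a member of the research team becomes aware of a severe adverse event, they will report this to the Chief Investigator", within 24 hours, and the sponsor is told. No attribution condition is attached.
- **Oversight.** The Trial Management Group and the TSC "will be informed of the details of all adverse events" (Safety monitoring). On the TSC, the section on oversight committees adds: "It has the ability to see unblinded adverse event data if it is perceived that the frequency of events is higher than anticipated".
- **Blinding.** "Participants will be not be blinded to group allocation as the intervention arm involves weekly one-to-one sessions with the Treating Therapist".
- **Contact during treatment.** The customised arm "will receive 12 individualised, 1 h, vestibular rehabilitation sessions over a 12 week period". The booklet arm has one one-hour session and two 15-minute calls, in weeks 1 and 4 (Generic booklet-based VR).

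**The concern.** A capture rule that depends on perceived cause does two things.

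First, it under-counts. A migraine, a neck pain or a spell of fatigue that the participant does not connect with VR is not reported under the stated rule, so nobody with clinical training judges whether it was related. The article itself treats exacerbation of migraine by the exercises as a possibility (Customised VR; Discussion), so such events are not remote.

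Second, the person applying the rule knows the allocation, and the two arms experience VR differently. One has weekly supervised sessions, with symptom-provoking exercises among the options. The other practises alone after one session. The same problem could be blamed on VR more readily in one arm than in the other.

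At stake are the interpretation of adverse event counts by arm and the information on which the TSC decides whether to look at unblinded data. The primary analysis of the Dizziness Handicap Inventory (DHI) is not affected. The analysis plan cannot repair the problem, because an event that was never captured is not there to analyse.

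**Working it through.** The safety section states no figure, so there is none to reproduce. The check has two parts.

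**1. Which events does the stated rule reach?**

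| Type of event | Condition for reporting | Depends on the participant's attribution? |
|---|---|---|
| Relapse | none | no |
| Fall | none (a prospective daily falls diary is also kept) | no |
| Severe adverse event | research team becomes aware | no |
| Any other new or worsening problem | participant perceives a link with VR | yes |

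Only the last row is affected. For the oversight bodies, being told of all events then means all that passed this condition, plus relapses, falls and the severe events the team learned of.

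**2. What does the rule do to counts?**

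For events in the last row, with p the true risk in an arm and a the probability that a participant with the event attributes it to VR:

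recorded risk = p × a

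recorded ratio = (p₁/p₂) × (a₁/a₂)

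The documents give neither p nor a. The values below are assumptions, chosen to show the range. The planned 35 per arm is from Sample size.

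*Loss with equal attribution.* Take a = 50% in both arms and the same true risk in both:
- p = 20%: 70 × 0.20 = 14 events, 7 lost
- p = 30%: 70 × 0.30 = 21 events, 10.5 lost
- p = 40%: 70 × 0.40 = 28 events, 14 lost

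The ratio stays at 1.0, but half the events are missing.

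*Distortion with unequal attribution.* Take p = 30% in both arms, so the true ratio is 1.0:

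| a₁ vs a₂ | Recorded risks | Recorded ratio | Lost, of 21 |
|---|---|---|---|
| 50% vs 50% | 15% vs 15% | 1.0 | 10.5 |
| 50% vs 25% | 15% vs 7.5% | 2.0 | 13.1 |
| 60% vs 20% | 18% vs 6% | 3.0 | 12.6 |
| 25% vs 50% | 7.5% vs 15% | 0.5 | 13.1 |

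In expected counts, the third row is 35 × 0.18 = 6.3 against 35 × 0.06 = 2.1. The last row is the second with the arms exchanged, because the direction is unknown.

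*Masking.* A true 30% vs 20% (ratio 1.5) with attribution of 40% vs 60% gives 0.30 × 0.40 = 12% against 0.20 × 0.60 = 12%. The recorded ratio is 1.0 and the true difference disappears.

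If every problem were recorded whatever its cause, a would equal 1 in both arms and the recorded ratio would equal the true ratio, apart from any difference in how often and how participants are asked.

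**The case against.** **Severe events are outside the rule.** A reader might infer that, relapses and falls apart, nothing is captured without the participant's attribution, and that investigator and TSC never see the rest. The documents do not support that. Severe events depend on the team's awareness, not on the participant's view, so the point is limited to non-severe problems.

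**Other data cover part of the gap.** The fatigue scale, the MS impact and walking scales, the DHI, the Vertigo Symptom Scale and the Dynamic Gait Index are collected in both arms at 14 and 26 weeks. Self-reported health and social care use is collected too, so an admission would be expected to show there. Concerns are also discussed at customised sessions and in the booklet calls. This stands as a partial offset. A scale score or a service count gives no event with an onset and a judgement of relatedness, and some problems, such as neck pain, have no dedicated scale.

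**No safety comparison is promised.** A reader might infer that a planned between-arm safety comparison is biased, perhaps against the customised arm. The aims, objectives and analysis sections state no such comparison. Both arms receive VR, so the condition applies to both, and nothing in the documents fixes which arm would attribute more. The ratios above are only the assumed attribution rates divided. What remains is that any tabulation by arm would carry an unknown factor. The TSC's trigger is described as event frequency, with unblinding afterwards, so under-capture bears on the trigger and differential attribution on what is seen after it.

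**Wording and proportionality.** The sentence speaks of reporting, the article condenses a fuller protocol, and it cites reviews that found VR safe. Selective capture of non-severe events can be defended as proportionate. But the rule is stated positively, it makes the participant's view of cause the criterion, and nothing else in the article says that problems failing it are kept.

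**Conclusion.** The point holds in a limited form. For non-severe problems other than relapses and falls, reporting depends on causal attribution by a participant who knows the arm. Problems not linked to VR go unreported. Counts by arm, and the frequency the TSC judges, are the product of occurrence and attribution.

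The identity in the working is exact for events under this rule. Its numerical effect is unknown: with the assumed rates shown, it runs from no distortion of the ratio but half the events lost, to a two- or three-fold spurious ratio in either direction, or to full masking of a true ratio of 1.5. The conclusion rests on reading the Safety monitoring sentence as the operative capture rule. It does not rest on any one attribution rate, and it does not establish that either arm's harms will be over- or under-stated relative to the other.

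**What to change.** Replace the sentence in Safety monitoring, and the matching adverse event form text, along these lines:

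*All new or worsening problems are recorded from randomisation to T26, whatever their perceived cause, using the same neutral prompt at the same scheduled times in both arms (at least T14 and T26). The participant's view of relatedness is recorded as a separate field. The Chief Investigator or a delegate assigns relatedness. All events, and related events, are reported by arm.*

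The common prompt and schedule are needed because removing the attribution condition alone would leave 12 supervised sessions against one session and two calls as unequal opportunities to report. Problems that come up at intervention contacts can still be recorded, but the comparison by arm should rest on the scheduled enquiries.

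Cost: more forms to complete and review in a trial of about 70 participants. Treatment, endpoints and sample size are unchanged. Trial status says that recruitment is under way, so participants before and after the change will have been observed under different rules. Record the date of the change and report events separately before and after it.

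### The 24-hour safety report is triggered by a 'severe' adverse event, a term of intensity, where a 'serious' one should be the trigger

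*Protocol article*

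**What the plan says.** The Safety monitoring section sets out three things.

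- **What is reported.** "New or worsening problems which participants perceive to be related to participation in VR, as well as any relapses and falls, will be reported". No intensity threshold applies to relapses and falls.
- **What is reported quickly.** "If a member of the research team becomes aware of a severe adverse event, they will report this to the Chief Investigator". The deadline for this report is 24 hours. The notice to the sponsor hangs on the same trigger and has no time limit of its own.
- **What reaches oversight.** "The Trial Management Group and the Trial Steering Committee will be informed of the details of all adverse events". No time limit is attached.

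The section on trial management and oversight committees adds that "The TMG consists of members of the research team with representation from the CTU and the trial Sponsor" and that "The TMG meets approximately monthly". The TSC meets about every 6 months and monitors adverse event reports. On unblinding it says: "It has the ability to see unblinded adverse event data if it is perceived that the frequency of events is higher than anticipated".

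**The concern.** Intensity and seriousness are different attributes of an adverse event, and expedited reporting is meant to follow seriousness. A rule keyed to intensity sorts events wrongly in both directions. A brief, intense bout of vertigo that settles without consequence meets the trigger. An event that puts someone in hospital, but is of mild or moderate intensity, does not.

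This matters in this population. The Background describes balance and mobility impairment leading to falls and injuries, and the customised programme includes exercises chosen because they bring on symptoms. Both kinds of misclassified event are therefore plausible. What is at stake is whether the Chief Investigator and the sponsor hear promptly of a serious event.

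**Working it through.** There is no figure to reproduce and no arithmetic applies. The check is a comparison of texts.

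**1. Is the trigger an intensity term in this document?** The article does not define 'severe adverse event', so its usage elsewhere is the best internal guide.
- The Background grades the impact of dizziness as moderate or severe and links greater severity to lower quality of life.
- The Randomisation section defines severity of dizziness by a cut-off of 59 on the Dizziness Handicap Inventory.
- The Discussion separates severe from less severe migraine when explaining who is excluded.

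Each use means intensity.

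**2. Does another rule cover seriousness?** No. The term 'serious adverse event' does not appear, and no seriousness criterion (death, threat to life, hospital admission, lasting disability) is stated as a reporting trigger. The 24-hour rule is the only adverse event route with a deadline.

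**3. What happens to each type of event under the literal rule?**
- *Serious and severe:* Chief Investigator within 24 h, sponsor informed.
- *Severe, not serious:* the same expedited route, without need.
- *Serious, not severe:* no 24-hour report and no linked sponsor notice. If recorded, its details go to the TMG and TSC.
- *Neither:* if recorded, to the TMG and TSC. This is appropriate.

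The third row is the defect.

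**4. How much is lost in the third row?** Speed. The TMG includes the sponsor and meets about monthly. On the assumption that details are passed on only at meetings, which the article does not say, notice could slip from 24 h to as much as about a month. If details are circulated sooner, the delay is shorter.

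**5. Why 'if recorded'?** The stated scope is problems that participants themselves link to the rehabilitation, plus relapses and falls. An admission following a relapse or fall is within scope. One outside those categories might not be captured on the article's wording, although the full protocol may be broader.

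**The case against.** The strongest reply has three parts.

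**The term may be defined elsewhere.** This is a journal article condensing a longer protocol, and event definitions are commonly left there. 'Severe' may be a slip for 'serious', or the full protocol may define it by outcome. The article also gives no mild/moderate/severe scale for adverse events, so nothing in it shows that staff would class a hospital admission as non-severe. This stands as a limit on the consequences: the failure depends on a literal reading, and a reconciliation of wording may be all that is needed. It does not remove the point. The article does not leave the rule out. It states trigger, recipient and deadline, and the trigger is the wrong term.

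**Other routes exist.** Relapses and falls are reportable at any intensity, and all adverse events go to the TMG and TSC. This stands. A reader might infer that serious events of lesser intensity would never reach the sponsor; the documents do not support that, because the sponsor sits on the TMG. Neither route has a time limit, however, so neither replaces the 24-hour report.

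**Wider consequences do not follow.** Two further inferences are tempting.
- A reader might conclude that expedited counts could not be interpreted by arm. The trigger is the same in both arms, and the article plans no comparison of expedited counts. The customised arm has more therapist contact (12 sessions against one session and two calls), which may affect how many events are noticed, but that would not make counts uninterpretable.
- A reader might conclude that the 24-hour trigger is the trial's main early safety signal, because the TSC looks at unblinded events only when frequency seems high. That provision concerns seeing data by arm. It does not govern whether events reach the committee, which monitors adverse event reports in any case.

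**Conclusion.** The point holds as an error in an operative safety rule. The only time-limited report is tied to intensity, so on a literal reading a serious event of mild or moderate intensity misses rapid notification to the Chief Investigator and the linked notice to the sponsor. Awareness through the TMG and TSC remains for any event that is recorded.

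The number of events affected cannot be estimated, since the article gives no rates by seriousness or intensity. The primary outcome, sample size and planned analyses are unaffected. The conclusion assumes that 'severe' carries its usual meaning, which the article's other uses support, and that the full protocol does not already define the term by outcome. If it does, the defect is confined to the published wording. Correction is still worthwhile, because it bears on participant safety, is nearly free, and recruitment was ongoing when the article appeared.

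**What to change.** - In the 24-hour rule, replace 'severe' with 'serious'.
- Reconcile the rule with the seriousness definition in the full protocol, and either state the criteria or point to where they are given.
- Record intensity as a separate item on the adverse event form, so that the two attributes are not confused again.

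The cost is a small wording change, a line on the form if it lacks one, and possibly a few more expedited reports. Some reports of intense but non-serious events would no longer be needed. No change to the design or analysis follows.
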